## Abstract

Children with Autism Spectrum Disorder (ASD) frequently experience psychomotor impairments, limited participation in physical activities, and reduced quality of life (QoL). Exercise shows promising benefits, but physiotherapy approaches in ASD are underreported, with limited evidence supporting a structured framework that systematically targets motor and functional outcomes. This study protocol describes a single-blinded randomised controlled trial evaluating the effectiveness of a structured physiotherapy intervention on motor skills, physical activity levels, and behavioural and QoL among children with mild to moderate ASD. This trial will include 64 children aged 6–10 years with ASD. Participants will be randomly assigned to an intervention group or a control group. Both groups will receive usual care therapy, equated between groups. The intervention group will also receive structured physiotherapy twice weekly for 12 weeks, each session lasting 60 min. The intervention integrates coordination, balance, strength, and endurance training. Outcome assessments will be conducted at baseline and post-intervention using validated instruments: GARS-3, BOT-2, GLTEQ, CBCL and PedsQL. Data analysis will follow the intention-to-treat principle and will examine between-group and within-group changes across all outcome measures. Qualitative data will be analysed using thematic analysis to characterise themes reflecting participants' engagement and parents' and caregivers' perspectives on the intervention.

## Specifications table

**Table utbl0001:** 

**Subject area**	Medicine and Dentistry
**More specific subject area**	Rehabilitation
**Name of your protocol**	Structured Physiotherapy Intervention
**Reagents/tools**	Gilliam Autism Rating Scale–3 (GARS-3), Bruininks-Oseretsky Test of Motor Proficiency–2 (BOT-2), Godin-Shephard Leisure-Time Exercise Questionnaire (GLTEQ), Child Behaviour Checklist (CBCL) and Pediatric Quality of Life Inventory (PedsQL).
**Experimental design**	This study employs a mixed-methods design integrating a randomised controlled trial (RCT) with semi-structured qualitative interviews involving children with ASD aged 6–10 years and their parents or caregivers.
**Trial registration**	This study protocol is registered with the International Standard Randomised Controlled Trial Number under the registration number ISRCTN34436540.
**Ethics**	Ethical approval was obtained from the National University of Malaysia’s Human Research Ethics Committee (JEP–2024–1127)
**Value of the Protocol**	Given the inconclusive results from the previous study, this protocol aims to provide essential evidence on the effectiveness of structured physiotherapy intervention by utilising robust outcome measures, including psychomotor and quality of life (QoL) among children with ASD. This study protocol will offer valuable guidance for clinicians on incorporating structured physiotherapy intervention into management for children with ASD, potentially enhancing therapeutic outcomes and improving patient care.

## Background

Autism Spectrum Disorder (ASD) affects approximately 1 in 36 children globally and represents a growing public health concern [1]. ASD is characterised by persistent difficulties in social communication and restricted, repetitive behaviours [2]. Beyond these core diagnostic characteristics, children with ASD commonly demonstrate motor impairments, including poor coordination, impaired balance, and delayed fine and gross motor skill development [3]. Evidence indicates that 80–88 % of children with ASD present motor impairments of clinical significance [4,5]. These motor impairments interfere with age-appropriate physical play, school-related movement tasks, and sport participation, which may reduce independence, limit peer interaction, and contribute to poorer overall quality of life (QoL) [6,7].

Neurobiological evidence supports the need for targeted motor rehabilitation [8]. Motor impairments in ASD are associated with altered cerebellar–cortical connectivity, contributing to deficits in balance control and motor planning [8]. Neuroimaging studies demonstrate reduced cerebellar volume and disrupted signalling between the cerebellum and the primary motor cortex, impairing implicit motor learning, a process typically acquired automatically through play in typically developing children [9]. Consequently, children with ASD more consistently benefit from structured programmes involving high repetition and explicit feedback, rather than unstructured motor practice alone [10].

A wide range of motor and exercise-based interventions has been evaluated in children with ASD, including fundamental motor skill programmes, yoga, rhythmic movement, aquatic therapy, exergaming, physical education, and general physical activity initiatives [[11], [12], [13]]. While these interventions show promising results, the evidence remains heterogeneous, with substantial variability in duration, frequency, supervision, instructor expertise, and progression criteria, limiting comparability and clarity about optimal treatment parameters [[11], [12], [13]]. Many programmes examine motor outcomes in isolation without evaluating broader functional pathways or QoL [14,15]. This leaves limited clarity about whether motor improvements translate into physical activity participation, behavioural gains, or QoL changes [[13], [14], [15]].

Despite its clinical relevance, physiotherapy remains underutilised in ASD management [7]. Physiotherapy provides an impairment-focused, clinically-led approach, applying motor learning strategies with task-oriented progression to improve movement quality and participation [16]. However, existing service utilisation statistics report high access to speech or occupational therapy, while fewer receive physiotherapy despite prevalent motor challenges [17]. Physiotherapy-led interventions for children with ASD remain poorly standardised and commonly consist of small or uncontrolled studies, limiting scalability or clinical translation [17,18]. Contributing factors include ASD being primarily perceived as a behavioural condition, limited specialist physiotherapy training, and low integration of physiotherapists within multidisciplinary care pathways [17,19].

This study protocol describes a single-blind RCT designed to evaluate a structured, progression-based physiotherapy-led motor intervention targeting motor impairments in children aged 6–10 years with mild to moderate ASD, assessed alongside physical activity, behaviour, and QoL. The trial includes caregiver-partnered interaction and a mixed-method evaluation to support implementation relevance. Evidence from this trial is expected to provide more precise clinical parameters and a replicable physiotherapy-led protocol. This may strengthen standardised motor-based intervention and support more consistent integration within existing ASD care pathways.

## Description of protocol

### Trial design

This study employs a mixed-methods research design, integrating a two-arm, parallel-group, single-blind randomised controlled trial (RCT) with semi-structured qualitative interviews involving children with ASD aged 6–10 years and their parents or caregivers. The primary aim is to evaluate the effectiveness of a structured physiotherapy intervention on psychomotor and QoL in children with mild to moderate ASD. The trial protocol was designed in accordance with the Consolidated Standards of Reporting Trials (CONSORT) 2010 and SPIRIT guidelines to ensure methodological rigour and transparency in reporting. This trial has been registered with the International Standard Randomised Controlled Trial Number under the registration number ISRCTN34436540.

### Study location

This multi-site trial will be conducted across two regions in Peninsular Malaysia, namely the East Coast Region in Terengganu and the Central Region in Kuala Lumpur. Participants will be recruited from community-based rehabilitation centres that provide services for children with ASD, operated in the two regions under the Ministry of Welfare, Malaysia. In Terengganu, recruitment will involve centres in three districts: Marang, Kuala Nerus, and Kuala Terengganu. In Kuala Lumpur, participants will be recruited from similar community-based centres and the Universiti Kebangsaan Malaysia (UKM) Specialist Children's Hospital. The intervention will be implemented at two primary sites: (1) the Physiotherapy Clinic, Faculty of Health Sciences, UKM, Kuala Lumpur, for participants from Kuala Lumpur, and (2) the Terengganu Autism Organisation Centre for participants from Terengganu.

### Sample size calculation

The sample size for this study was calculated using G*Power software version 3.1.9.4, employing an F-test for repeated-measures analysis of variance (ANOVA) with a within–between interaction [20]. The calculation was based on an alpha level of 0.05, a statistical power of 80 % (1–β = 0.80) and an effect size (f) of 0.12. This effect size was derived from the previous study [21] which investigated motor skill outcomes using the BOT-2 which is the primary outcome measure in the present study. The Cohen’s d reported in the previous study [21] was converted to Cohen’s f using the online tool provided by https://www.escal.site/. Based on these parameters, the minimum required sample size was calculated to be 58 participants. Additionally, accounting for an anticipated dropout rate of 10 % the required sample size is 64 participants, with 32 participants allocated to each group.

### Inclusion and exclusion criteria

Participants will be selected based on specific inclusion and exclusion criteria to ensure the sample is relevant. The inclusion criteria are as follows: (i) aged between 6 and 10 years old, (ii) have a confirmed diagnosis of ASD according to the DSM-5-TR, (iii) classified as having mild to moderate severity based on the GARS-3 autism index (55–100; level 1–2). (iv) demonstrate motor difficulties on the BOT-2 Short Form (iv) able to follow simple verbal instructions (v) have written informed consent provided by a parent or legal guardian. The exclusion criteria include (i) having sensory or physical impairments that would limit their ability to participate in the intervention, (ii) other neurological or developmental conditions such as epilepsy or cerebral palsy, or if they have physical disabilities arising from head injury or other acquired conditions, (iii) having co-occurring diagnosis such as Attention Deficit Hyperactivity Disorder and Down Syndrome, (iv) currently involved in another clinical trial or intensive motor programme, and (v) unstable medical conditions or recent changes in medical treatment.

### Participant screening, recruitment and randomisation

All children with ASD will be screened and recruited from the sampling frame of participating centres, using simple random sampling. The screening, recruitment, and randomisation procedures will be conducted by an independent researcher who is not involved in data collection or outcome assessment. Screening assessments of GARS-3 and BOT-2 Short Form will be conducted before randomisation to determine eligibility. As these assessments will be administered immediately before group allocation and under the same standardised conditions required for baseline measurement, the screening scores will be used as baseline data to minimise participant burden and avoid unnecessary repetition of measures. Eligible participants and their caregivers will receive clear, comprehensive information about the study through written materials and verbal explanations. This will include the study objectives, procedures, potential risks and benefits, and the anticipated time required for participation. After confirming their understanding, parents or legal guardians will be asked to provide written informed consent. Assent will also be obtained from the participating children in accordance with ethical standards for research involving minors. Only children classified as having mild to moderate ASD according to the GARS-3 will be invited to attend a motor skills assessment using BOT-2 Short Form. If a selected participant declines, the next name on the list will be contacted to achieve the desired recruitment target. Screening will take place over a two-week period, during which eligibility will be confirmed. Following confirmation of eligibility, participants will be randomised into either the intervention or control group using a computer-generated randomisation sequence (randomization.com). To reduce potential confounding, stratified randomisation will be applied by age group (6–8 years vs. 9–10 years) and ASD severity (mild vs. moderate, based on GARS-3). This approach will balance participant characteristics across study arms and ensure that outcomes reflect the intervention's effect independent of these variables. Allocation concealment will be maintained to prevent selection bias. Children who are successfully randomised will then be scheduled for baseline parent proxy assessments, conducted before the initiation of the intervention. GARS-3 and BOT-2 Short Form scores obtained during screening will serve as baseline values, while the GLTEQ, CBCL, and PedsQL will be administered as parent-proxy assessments following randomisation but before the intervention begins. All five outcome measures will be re-administered at post-intervention. This sequence ensures that group allocation is unbiased and that baseline data reflect participants’ pre-intervention status. A SPIRIT schedule of enrolment, interventions, and assessments is shown in Fig. 1.

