### Data analysis

Data will be analysed using IBM SPSS Statistics Version 28. Descriptive statistics will summarise participant characteristics, and baseline comparability between groups will be evaluated using independent *t*-tests or chi-square tests. All analyses will follow the intention-to-treat (ITT) principle, with missing data handled using last observation carried forward (LOCF) and will be supported by sensitivity analyses using multiple imputation. A 2 × 2 mixed-design ANOVA (group × time) will examine within and between-group differences across the intervention period. Significant interactions will be examined using Bonferroni-adjusted post hoc tests. Effect sizes will accompany all significance tests, including Cohen’s d for mean differences and partial eta squared (η²p) for ANOVA effects, with 95 % confidence intervals reported. Statistical significance will be set at *p* < 0.05. Qualitative data will be analysed using thematic analysis following Braun and Clarke’s six-phase protocol [35].

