### Strengths and limitations

This study has notable strengths, including the use of a structured physiotherapy intervention grounded in established motor and behavioural frameworks, as well as a mixed-methods approach that integrates quantitative outcomes with qualitative insights. However, several limitations should be considered. Parent-reported measures such as the PedsQL, CBCL, and GLTEQ may be influenced by subjective perceptions or social desirability. Usual-care practices in the control group may vary across centres and therapists, introducing unavoidable heterogeneity. Additionally, the sample is limited to children aged 6–10 years with mild to moderate ASD, which restricts generalizability to other age groups or severity levels. Findings should therefore be interpreted within the context of this defined population.

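### Randomisation is stratified by age group and autism severity, but the stated group-by-time ANOVA omits both; this wastes precision only if the strata predict change

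*Protocol article*

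**What the plan says.** In the protocol article, under Participant screening, recruitment and randomisation, "stratified randomisation will be applied by age group" (6–8 versus 9–10 years) and by GARS-3 severity (mild versus moderate), which makes four strata. The stated purpose is to reduce confounding and balance the arms.

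Under Data analysis, the named model is a two-by-two mixed ANOVA of group and time, which "will examine within and between-group differences across the intervention period". No stratification factor and no region term is listed. Sample size calculation rests on the same test, "employing an F-test for repeated-measures analysis of variance (ANOVA) with a within–between interaction".

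Region is not a stratification factor. Under Study location, "The intervention will be implemented at two primary sites", one in each region. Under Strengths and limitations, "Usual-care practices in the control group may vary across centres and therapists".

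**The concern.** Stratified allocation removes between-stratum variation from the treatment comparison. An analysis that ignores the strata puts that variation back into the error term. Where the strata predict the quantity being analysed, the standard error is then larger than the design warrants, the true type I error falls below the nominal 5%, and precision that the randomisation has already secured is not used.

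The sponsor chose these two factors as ones worth balancing, and the article fixes both the factors and the dimensions of the model, so design and analysis do not match as written. What is at stake is efficiency. The question is how much, for the test actually planned.

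**Working it through.** **1. What the planned test is.** With two groups and two time points, the group-by-time F-test is the two-sample t-test on D = post − pre. A stable effect of age or severity on the score level is in both measurements and cancels from D. Only an effect on change remains in the error.

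**2. Inputs from Sample size calculation.** "The calculation was based on an alpha level of 0.05", "a statistical power of 80" per cent and "an effect size (f) of 0.12". The minimum N is 58, raised to 64 for dropout. The pre-post correlation ρ is not stated.

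**3. Reproducing the stated 58.** λ = N·m·f²/(1 − ρ), with m = 2, df1 = 1 and df2 = N − 2.
- Assumed ρ = 0.80: λ = 58 × 2 × 0.0144 / 0.20 = 8.352; power 0.811; required N is 58.
- Assumed ρ = 0.70: required N is 84; power at 58 is 0.640.
- Assumed ρ = 0.50: required N is 140; power at 58 is 0.435.

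So ρ = 0.80 is used below because it reproduces the article's figure, not because the article states it.

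**4. Adding the two strata to the model for change.** Let R² be the share of change variance that they explain (not given; a range is shown). Then λ becomes λ/(1 − R²), df2 becomes N − 4, and the interval width is multiplied by √(1 − R²).

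| R² | λ at N = 58 | Power, N = 58 | Power, N = 64 | Interval narrower by |
|---|---|---|---|---|
| strata not in model | 8.352 | 0.811 | 0.848 | – |
| 0 | 8.352 | 0.810 | 0.848 | 0% |
| 0.05 | 8.352/0.95 = 8.79 | 0.829 | 0.865 | 2.5% |
| 0.10 | 8.352/0.90 = 9.28 | 0.849 | 0.883 | 5% |
| 0.20 | 8.352/0.80 = 10.44 | 0.888 | 0.916 | 11% |

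The last column does not depend on ρ. The power figures do. At ρ = 0.70 and N = 58, power is 0.640 unadjusted and 0.662, 0.685 and 0.736 adjusted for R² of 0.05, 0.10 and 0.20. At ρ = 0.50 it is 0.435, then 0.453, 0.473 and 0.519.

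**5. Simulation of the stratified design.** N = 58, ρ = 0.80, blocks of 4 within strata (block size assumed), 6,000 runs per setting; simulation error on the type I error is about 0.003.

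| Strata explain | Type I error, unadjusted / adjusted | Power, unadjusted / adjusted |
|---|---|---|
| level only | 0.050 / 0.052 | 0.803 / 0.800 |
| 5% of change | 0.048 / 0.051 | 0.817 / 0.829 |
| 10% of change | 0.042 / 0.054 | 0.824 / 0.848 |
| 20% of change | 0.029 / 0.049 | 0.828 / 0.883 |

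The balance produced by stratified allocation gives the unadjusted test slightly more power than the formula's 0.811. The gain from adjustment under the actual design is therefore about 1, 2 and 5.5 points.

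**6. How the strata must enter.** With complete data at two times, a covariate main effect acts only on the average of the two scores. The group-by-time contrast acts only on their difference. In a numerical check, adding main effects alone left both the estimate (0.3714) and its standard error (0.1514) unchanged. Stratum-by-time terms, or an ANCOVA of the post score, are needed to change the test.

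**The case against.** The strongest reply is that the unadjusted analysis is valid. It is at worst conservative, and its cost is zero when age and severity affect level only. Nothing in the documents says that either factor predicts change. Under Outcome measures, BOT-2 standard scores use age-specific norms, which weakens age as a predictor of the primary outcome. Covariate lists are also commonly left to an analysis plan, which is not shown here.

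Most of this stands. It limits the point to efficiency and makes the size unknown, but it does not remove the mismatch, because the article names the full model. Nor is the level-only case a safe assumption for every outcome. GARS-3 is both a stratifier and a secondary outcome, and its screening score serves as its baseline. Children placed in the higher stratum by that score can be expected to drift back towards the mean, so severity is likely to predict GARS-3 change even without treatment.

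A reader might also infer that leaving out region biases the result, since region determines the treatment site and usual care may differ by centre. The documents do not support that. Region is not a stratum, so omitting it does not misstate the standard error. A stable regional difference cancels from change. Imbalances can occur: with 64 children split evenly between regions (assumed) and allocated 32:32 without regard to region, the arms would differ by 6 or more children from one region in about 21% of randomisations. But that is chance variation, which the interval and the stated alpha already cover.

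**Conclusion.** The concern holds as a minor mismatch between design and analysis. Two stratification factors are omitted from the stated model. For the planned interaction test, the cost runs from nothing (strata affect level only) to intervals about 2.5%, 5% or 11% wider than needed, set against the adjusted power of about 0.83, 0.85 or 0.89 in place of 0.81, if the strata explain 5%, 10% or 20% of change variance. These figures assume ρ = 0.80 and N = 58; R² is unknown.

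It would be too strong to say that power is certainly lost, that the treatment effect is biased, or that type I error is inflated. The error, where there is any, is on the conservative side. The unstated correlation matters far more to power than the omitted strata do. The case for changing the model is that the change is nearly free, not that the stated analysis is invalid.

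**What to change.** State that each outcome is analysed by ANCOVA of the post-intervention score on baseline score, group, age group and GARS-3 severity stratum, with the strata coded as used at randomisation. If the repeated-measures model is kept, add age-group-by-time and severity-by-time terms; main effects alone would leave the test as it is. Region may be added as an optional precision covariate, specified in advance.

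The table in the working is for the change-score model with strata. Any further precision from the baseline term in the ANCOVA is not counted there.

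Cost: two degrees of freedom, or three with region. If the covariates explain nothing, power at N = 58 and ρ = 0.80 moves from 0.8106 to 0.8101 with two and to 0.8098 with three, which is under 0.1 percentage point. All the variables are known at randomisation, so no new data are needed. Under Protocol validation, the article says that outcome assessments have not begun, so the change can still be made in advance.

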### Blinding

A single-blind approach will be employed. Outcome assessors will remain blinded to group allocation to minimise bias in outcome ascertainment. Participants and therapists cannot be blinded due to the nature of the intervention. The success of assessor blinding will be assessed by asking the blinded outcome assessor to guess the participant’s group allocation as intervention, control or unsure after each assessment. Responses will be summarised descriptively and quantified using Bang’s Blinding Index [22].

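### Baseline GLTEQ, CBCL and PedsQL come from parents after randomisation; if the parents already know the allocation, the baseline of three secondary outcomes can differ by arm

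*Protocol article*

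**What the plan says.** The section on participant screening, recruitment and randomisation fixes a different baseline time for two sets of instruments.

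- For two of the five: "Screening assessments of GARS-3 and BOT-2 Short Form will be conducted before randomisation to determine eligibility". Those scores then serve as baseline.
- For the other three: "Children who are successfully randomised will then be scheduled for baseline parent proxy assessments, conducted before the initiation of the intervention". The section repeats that GLTEQ, CBCL and PedsQL "will be administered as parent-proxy assessments following randomisation but before the intervention begins".

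The section gives this reason for the order: "This sequence ensures that group allocation is unbiased and that baseline data reflect participants’ pre-intervention status". On concealment it says "Allocation concealment will be maintained to prevent selection bias". It does not say when families are told their arm.

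The Blinding section keeps outcome assessors blind but states: "Participants and therapists cannot be blinded due to the nature of the intervention".

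Under Outcome measures, motor skill (BOT-2 Short Form) is primary; physical activity, behaviour and QoL are secondary. Under Data analysis, the test is a 2 × 2 group × time mixed ANOVA, under intention to treat, with LOCF for missing data and multiple imputation as sensitivity analysis.

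**The concern.** On a parent-proxy form the parent is the rater, so a blinded assessor who hands over the questionnaire does not protect the answers. A parent who has just learned that the child will, or will not, get the programme may rate activity, behaviour or QoL differently from a parent who does not know. That would turn a baseline that randomisation should balance into one that can depend on the arm.

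Being collected before the intervention rules out an effect of treatment. It does not rule out an effect of knowing the allocation. The Strengths and limitations section accepts that these three instruments are open to subjective perception and social desirability, but does not consider that at baseline this could differ between arms.

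At stake are three of the four secondary outcomes. There is also a missing-data consequence: a family that withdraws after randomisation but before the forms are completed has no value on these three scales.

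**Working it through.** **Reading the order.** The text gives the sequence twice: randomise, then parent-proxy baseline, then intervention. Concealment is mentioned only against selection bias, which concerns who enters which arm. It is not a statement that parents stay unaware afterwards. No reason is given for placing three questionnaires later than the other two instruments. The burden argument in that section is about not repeating GARS-3 and BOT-2, and it does not apply here.

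**How a shift reaches the result.** With two time points, the group × time interaction is the between-arm difference in change (post minus baseline). Suppose knowledge of allocation moves the reported baseline by s SD between arms, and a fraction k of that shift is still present at post-intervention. With no true effect, the interaction then estimates

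k·s − s = −(1 − k)·s.

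A fully transient shift (k = 0) passes through one for one with opposite sign. A fully persistent shift (k = 1) cancels.

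**Illustration.** The plan states no figure on this point, so there is none to reproduce.

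Inputs from the documents:
- 32 per arm (Sample size calculation)
- two-sided α = 0.05 (Data analysis; two-sided assumed)

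Assumed, because the documents give neither:
- the net shift b = (1 − k)·s
- the baseline–post correlation ρ

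Formulas, with unit SD at each time:
- SD of change = √(2(1 − ρ))
- standard error of the difference in change = √(2(1 − ρ)) × √(2/32) = √(2(1 − ρ)) × 0.25
- noncentrality = b / standard error; noncentral t with 62 df

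For b = 0.2:
- ρ = 0.5: SD of change 1.00, SE 0.25, noncentrality 0.2/0.25 = 0.80, false-positive rate 12.4%
- ρ = 0.8: SD of change 0.632, SE 0.158, noncentrality 0.2/0.158 = 1.26, false-positive rate 23.8%

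| Net shift b (SD) | ρ = 0.5 | ρ = 0.7 | ρ = 0.8 |
|---|---|---|---|
| 0.1 | 6.8% | 8.0% | 9.5% |
| 0.2 | 12.4% | 17.4% | 23.8% |
| 0.3 | 21.9% | 33.2% | 46.3% |

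If half of a 0.2 SD shift persists, the net shift is 0.1 SD and the first row applies. Adjusting for baseline by ANCOVA instead would reduce the bias from a transient shift to ρ·s (0.10 SD for s = 0.2 and ρ = 0.5) but would not remove it.

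**With the forms before randomisation.** Allocation does not yet exist when the parent answers. The expected shift from this source is 0 and its contribution to the error rate is nil. The sample size does not change.

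**Withdrawal before the forms.** LOCF needs an earlier value. For GLTEQ, CBCL and PedsQL there is none. For BOT-2 Short Form and GARS-3 there is one, taken at screening.

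**The case against.** Several points on the other side are sound.

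- **Disclosure time is not stated.** The article dates randomisation, not the moment at which parents learn the arm, and the schedule figure is not available here. A site could complete the forms first and disclose afterwards. This stands, and it makes the bias conditional. It does not rescue the order, because nothing commits the sites to delayed disclosure.
- **Same raters at both times.** The same parents rate before and after, so a reporting shift that persists cancels in the change contrast. This stands; only the transient part matters.
- **Direction is unknown.** Disappointed control parents who rate low at baseline and later recover would bias against the programme; other reactions would favour it.
- **The primary outcome is not exposed.** BOT-2 Short Form, on which the sample size rests, has a pre-randomisation baseline, as does GARS-3. Trial design names QoL in the primary aim, but Outcome measures makes it secondary.
- **Parents are unblinded at post-intervention anyway.** That is true. It is a separate limitation, which reordering the forms does not cure.

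A reader might go further than the text allows in two places. One is to infer that the article calls this baseline unbiased. The justifying sentence applies that word to the allocation; of the baseline it says only that it reflects status before the intervention, which is correct for the planned order. The other is to infer that a family withdrawing early drops out of the intention-to-treat analysis. It remains in the BOT-2 Short Form and GARS-3 analyses and could be included for the other three scales by the planned multiple imputation, though without its own baseline on those scales.

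**Conclusion.** The point holds in conditional form. The order of procedures is explicit, and it leaves the baseline of three secondary outcomes open to knowledge of allocation without any stated benefit. Confidence in that is high. Whether bias follows depends on parents knowing the arm when they answer and on at least part of the shift fading by post-intervention. Confidence in that is medium.

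The figures of about 12% and 24% describe one assumed scenario (transient 0.2 SD, ρ of 0.5 and 0.8, no true effect, 32 per arm). They are not an expected error rate for this trial, and the documents do not support reading them as one. Under LOCF, the three outcomes also lose any family that leaves before the forms are completed. As only secondary outcomes are exposed, this is something that should be fixed rather than a defect that undermines the trial's main result.

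**What to change.** 1. For families not yet randomised, have GLTEQ, CBCL and PedsQL completed after consent and confirmation of eligibility, and randomise only once all five baselines are recorded.
2. For families already randomised, record whether each form was completed before or after the family learned the allocation.
3. Add a sensitivity analysis of the three outcomes that compares post-intervention scores without the post-randomisation baseline. It complements the change analysis but cannot replace it. It is free of the baseline shift, but a reporting difference that persists to post-intervention does not cancel in it. Its standard error at 32 per arm is 0.25 SD, against 0.158 SD for change at ρ = 0.8 (equal at ρ = 0.5).
4. Reword the sentence that justifies the sequence, so that it cannot be read as saying that the parent-reported baseline is protected from knowledge of allocation.
5. In Strengths and limitations, mention the baseline timing for children already enrolled, and keep unblinded parent rating at post-intervention as a separate limitation.

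Cost: a short amendment, a small reordering of visits within a staged screening process, and some forms from families who are not later randomised. The Protocol validation section says that recruitment and delivery are under way, so item 1 protects only later families.
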